## Methods

### Study aims

To perform a randomised controlled multicentre trial (RCT) in infants aged less than 12 months (corrected age) with clinically diagnosed bronchiolitis comparing HFNC therapy to standard subnasal oxygen therapy. The primary outcome is treatment failure of HFNC therapy or standard subnasal oxygen.

Secondary outcome measures comprise (a) the rate of transfer of children to higher level care (that is, the rate of transfer from regional hospitals to tertiary centres and rate of transfer from tertiary hospitals to their onsite intensive care unit (ICU) if the primary admission is to their tertiary hospital); (b) length of stay in hospital and (c) health care costs associated with the therapy, transfer and ICU admission (including intubation rates), and overall length of stay; (d) length of oxygen therapy; (e) and measurement of adverse side effects. We hypothesise that HFNC therapy will have a lower failure proportion, reduced transfer rate, reduced length of stay, and lower health care costs associated with the treatment, in comparison to standard subnasal oxygen.

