### Secondary outcome definition

Secondary outcomes are defined as (a) the proportion of infants requiring transfer to higher acuity care, which includes admission to an on-site paediatric intensive care or transfer to a tertiary hospital; (b) length of hospital stay, including intensive care length of stay and (c) intubation rates; (e) associated health care costs for the respective therapy; (f) length of oxygen therapy and; (g) adverse events.

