#### Escalation of therapy after treatment failure (primary outcome)

Once failure criteria are met, escalation of treatment may be from standard subnasal oxygen therapy to HFNC therapy and/or escalation to non-invasive ventilation or intubation and mechanical ventilation in intensive care. It is at the discretion of the attending physician to manage and treat the ongoing care. If escalation from standard subnasal oxygen to HFNC therapy occurs then the same protocol shall be applied as in HFNC therapy arm. However, at any time during the study the physician can override and escalate care. This aspect of clinical reasoning to escalate will be captured in the data set and is defined as follows: i.) increased work of breathing requiring escalation of respiratory support, ii.) decreased conscious level, iii.) deterioration of cardiovascular function with impaired peripheral perfusion, iv.) clinical judgment of attending (senior) medical officer triggers escalation of treatment and care.

With any escalation of treatment the nurse/patient ratio will be captured to perform cost assessments on required level of care at the time of escalation and thereafter.

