#### Data analysis

Descriptive statistics will be utilised to report on the baseline characteristics of the total study cohort, as well as by site. The primary outcome measure investigating clinical treatment failure will be analysed using test of two proportions, and will be reported as the difference, 95 % confidence interval and *p*-value. The secondary outcome measure investigating length of stay will likely be non-normally distributed, and as such will be analysed using a Mann-Whitney U test; if it is normally distributed independent samples t-test will be used. Analysis of secondary outcomes includes both comparisons of measurements and proportions, using confidence intervals of differences as the major method of presentation where possible. A logistic regression analysis will be used to identify risk factors. All analyses will be by intention-to-treat. A per protocol analysis will be undertaken as a secondary analysis. Pre-specified sub-groups include; ex-preterm infants, infants with congenital heart defect, infants less than 3 months of age (corrected), infants less than 6 months of age (corrected), infants presenting to tertiary sites, infants presenting to secondary sites. Statistical significance will be set at the 0.05 level. No interim analysis will occur and no stopping rules were defined.

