## Discussion

This large multicentre randomised trial will allow the definitive assessment of the efficacy of high flow nasal cannula therapy as compared to standard subnasal oxygen in preventing treatment failure and the need for escalation of respiratory support. This study will in addition provide a unique insight into the adverse events profile of high flow nasal cannula therapy when used outside the intensive care setting and the epidemiology of the moderate to severe end of the spectrum of bronchiolitis.

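### Adverse events are analysed only by allocated arm although failing controls may receive HFNC, so the promised HFNC adverse-event profile is only partly delivered

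*Protocol article*

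**What the plan says.** The Data analysis section of the protocol article sets one rule, without an exception for safety: "All analyses will be by intention-to-treat". It names one other analysis set: "A per protocol analysis will be undertaken as a secondary analysis".

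Adverse events fall under that rule. Secondary outcome definition ends its list with "f) length of oxygen therapy and; (g) adverse events", and Study aims lists "e) and measurement of adverse side effects".

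The escalation section says that, once failure criteria are met, "escalation of treatment may be from standard subnasal oxygen therapy to HFNC therapy and/or escalation to non-invasive ventilation or intubation" is possible. It adds: "If escalation from standard subnasal oxygen to HFNC therapy occurs then the same protocol shall be applied as in HFNC therapy arm". The physician may also escalate at any time on clinical judgement. Under Time frame, participation ends at death or discharge home, so the period after rescue lies within follow-up.

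The Discussion says that the trial will offer "unique insight into the adverse events profile of high flow nasal cannula therapy when used outside the intensive care setting".

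**The concern.** Read together, these sections mean that a pneumothorax, apnoea or bradycardia in a control infant on rescue HFNC is tabulated as a standard-oxygen event. The same infant is absent from the HFNC column. Rescued controls are those who deteriorated, so they are a group in whom the safety of HFNC outside intensive care is of particular interest.

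The per-protocol analysis does not clearly repair this. Rescue HFNC is permitted by the protocol, so a rescued control either stays in the control group or is dropped. Neither choice places the event under HFNC.

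At stake is the safety description of HFNC and how the between-arm difference in adverse events is read. The primary outcome and the sample size are not affected.

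**Working it through.** **1. The plan's own figure.** The Sample size section uses 10% v 5%, 90% power and type I error 0.05. With the two-sided pooled formula, n = [1.960·√(2·0.075·0.925) + 1.282·√(0.10·0.90 + 0.05·0.95)]² / 0.05², which gives 582 per group. This matches the protocol. The total is 1164. The recruitment target of 1400 implies attrition of 1 − 1164/1400 = 16.9%, within the stated 10–20%. I use 700 per arm (1400 at 1:1).

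**2. How many controls might receive HFNC.** Inputs from the Sample size section are f = 10% (planned failure of standard therapy, defined as transfer or PICU admission) and f = 16.7% (80/478, the 2011 transfer rate). The share s of failures rescued with HFNC is not in the document; I assume 25%, 50% and 100%.

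Rescued controls = 700·f·s. Share of all HFNC-exposed infants = 700·f·s / (700 + 700·f·s) = f·s / (1 + f·s), which does not depend on the arm size.

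| f | s = 25% | s = 50% | s = 100% |
|---|---|---|---|
| 10% | 17.5 (2.4%) | 35 (4.8%) | 70 (9.1%) |
| 16.7% | 29.2 (4.0%) | 58.5 (7.7%) | 116.9 (14.3%) |

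So in these scenarios about 86–98% of HFNC-exposed infants are still in the allocated HFNC arm.

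**3. Effect on the allocated-arm difference (illustration).** The event risks are assumptions, since the document gives none: r0 = 1% on standard oxygen and r1 = 2% on allocated HFNC, a true difference of 1.0 percentage point. Let rr be the risk during rescue HFNC, added to the 1% already carried. Allocated-arm difference = r1 − (r0 + f·s·rr), in percentage points:

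| f | s | rr = 2% | rr = 6% | rr = 10% |
|---|---|---|---|---|
| 10% | 25% | 0.95 | 0.85 | 0.75 |
| 10% | 50% | 0.90 | 0.70 | 0.50 |
| 10% | 100% | 0.80 | 0.40 | 0.00 |
| 16.7% | 100% | 0.67 | 0.00 | −0.67 |

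If rescued infants instead carry 2% in total, the difference is (r1 − r0)(1 − f·s). That is 0.95 for 10% with half rescued, 0.90 for 10% with all rescued, and 0.83 for 16.7% with all rescued. The distortion is small when few infants are rescued. It removes or reverses the difference only if most failures are rescued and their risk is high.

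**4. Escalation in the other arm.** HFNC-arm infants who fail also escalate; the planned 5% is 35 of 700. Let g and u be the shares of the HFNC and control arms that go beyond HFNC to ventilation, and v the event risk afterwards. The allocated-arm difference then gains (g − u)·v. The Background says that ventilation carries more adverse events, so v may be material. The sign of g − u is not known from the document, so step 3 does not settle the net direction.

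**5. Can events be reattributed?** Clinical observations requires oxygen or FiO2 and the high-flow rate at each set of observations. Therapy in use at onset should therefore be recoverable, provided that the event time is recorded.

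**The case against.** The strongest reply is that intention-to-treat is not a mistake here. The control strategy is standard oxygen with HFNC available on failure, and comparing by allocation validly contrasts it with HFNC first. That stands, and the allocated-arm comparison should stay.

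It can also be said that tables by treatment received are usually left to the analysis plan, which is not shown, and that nothing forbids one. That is fair as to detail. But this article does state a rule for all analyses and names only one further set, and an analysis plan that followed it would carry the gap forward.

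Three stronger readings might be inferred, and the documents do not support them:

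- **That an HFNC safety objective is not met.** Neither the listed aim nor the listed outcome is specific to HFNC; the HFNC profile appears only in the Discussion. About 700 infants allocated to HFNC still supply one. Rescue HFNC is optional, and any given in intensive care lies outside the setting that the Discussion names.
- **That the counting rule necessarily favours HFNC.** That follows for the control-to-HFNC crossover alone, and only if HFNC raises the risk. Events after HFNC-arm infants escalate to ventilation are counted against HFNC.
- **That the trial loses substantial power to detect harm.** The protocol gives no event risks and is powered on treatment failure. Crossover of 20–30% of controls would exceed both 10% and 16.7%, and 10% already requires every planned failure to be rescued with HFNC. Ward escalation to HFNC needs neither transfer nor PICU admission, so actual crossover could differ in either direction, but the document provides no higher figure.

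**Conclusion.** The point holds in a limited form. The stated rule places events on rescue HFNC under standard oxygen and leaves rescued controls out of the HFNC profile, which is therefore only partly delivered. On the protocol's rates and an assumed 25–100% rescue share, the omitted group is about 18–70 infants (2–9% of those exposed) at 10% failure, or about 29–117 (4–14%) at 16.7%. Its importance lies more in who these infants are than in their number. The narrowing of the apparent difference is conditional on HFNC raising the risk, and the net direction is open. Efficacy conclusions are unaffected, and the change is worth making because it is cheap.

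**What to change.** In Data analysis, keep intention-to-treat for efficacy and as the randomised safety comparison. Add a pre-specified descriptive safety table by therapy in use at event onset, with four categories:

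- standard oxygen before any HFNC;
- allocated HFNC;
- rescue HFNC in control infants, shown separately inside and outside intensive care;
- after escalation beyond HFNC.

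Give the infants exposed, the events and the time on each therapy. Base the Discussion's statement about the HFNC adverse-event profile on this table.

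The cost is a sentence or two of wording and one extra table. Little or no new data should be needed, but confirm that the case report form holds the event time. The drawback is that the table is not a randomised comparison, because rescued infants are selected for severity, and it must be labelled descriptive. Fixing it in advance also avoids choosing the safety presentation after the results of an open-label trial are known.

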### Adverse events and monitoring/reporting

#### Data safety monitoring

An external data safety monitoring board has been established. All adverse events and experiences by either staff or parent/guardian will be reported on the CRF provided for each patient and the local Principal Investigator notified who will in turn notify the Chief Investigator. A serious adverse event (SAE) is defined as any event that is fatal, life-threatening, permanently disabling, incapacitation or prolongs a hospital stay.

#### Reporting SAE

SAEs will be reported within 24 hrs by telephone to the local Principal Investigator who in turn will notify the Chief Investigator. The local site investigator will report the SAE to their local ethics committee within 48 hours (or in accordance with local ethics committee regulations).

#### Limitations

As a non-blinded trial there is the potential for the investigator to unintentionally introduce measurement or reporting bias because further knowledge of the study and treatment allocation could influence the clinicians’ decision-making. The end points can be seen as subjective and we cannot alter the medical and nursing staff’s opinion at certain points in the trial. As an example, some patients may be seen as not responding to enrolled arm treatment at one centre or on one shift whereas another centre or the next shift of staff may view this differently. It is not possible in this trial to blind the investigators or treating physicians.

#### Current status of trial

The study enrolment has commenced, and are expecting all 17 sites to be recruiting by end of July 2015.

## Discussion

This large multicentre randomised trial will allow the definitive assessment of the efficacy of high flow nasal cannula therapy as compared to standard subnasal oxygen in preventing treatment failure and the need for escalation of respiratory support. This study will in addition provide a unique insight into the adverse events profile of high flow nasal cannula therapy when used outside the intensive care setting and the epidemiology of the moderate to severe end of the spectrum of bronchiolitis.

### Time plan

To date (July 2015), 380 patients have been recruited for the planned 1400 patients with recruitment to be completed in 2017.
